## Abstract

**Background:**

Mental health problems are a significant social issue that have multiple consequences, including broad social and economic impacts. However, many individuals do not seek assistance for mental health problems. Limited research suggests martial arts training may be an efficacious sports-based mental health intervention that potentially provides an inexpensive alternative to psychological therapy. Unfortunately, the small number of relevant studies and other methodological problems lead to uncertainty regarding the validity and reliability of existing research. This study aims to examine the efficacy of a martial arts based therapeutic intervention to improve mental health outcomes.

**Methods/design:**

The study is a 10-week secondary school-based intervention and will be evaluated using a randomised controlled trial. Data will be collected at baseline, post-intervention, and 12-week follow-up. Power calculations indicate a maximum sample size of *n* = 293 is required. The target age range of participants is 11–14 years, who will be recruited from government and catholic secondary schools in New South Wales, Australia. The intervention will be delivered in a face-to-face group format onsite at participating schools and consists of 10 × 50–60 min sessions, once per week for 10 weeks. Quantitative outcomes will be measured using standardised psychometric instruments.

**Discussion:**

The current study utilises a robust design and rigorous evaluation process to explore the intervention’s potential efficacy. As previous research examining the training effects of martial arts participation on mental health outcomes has not exhibited comparable scale or rigour, the findings of the study will provide valuable evidence regarding the efficacy of martial arts training to improve mental health outcomes.

**Trial registration:**

Australian New Zealand Clinical Trials Register ACTRN12618001405202. Registered 21st August 2018.

## Background

Mental health problems are a significant social issue that have multiple consequences; ranging from personal distress, disability, and reduced labour force participation; to wider social and economic impacts. The annual global cost of mental health problems was estimated as $USD 2.5 trillion by the World Health Organisation [1]; and the annual cost of mental illness in Australia has been estimated as $AUD 60 billion [2]. These costs are projected to increase 240% by 2030 [1].

However, for a variety of reasons including stigmatisation of mental health and the cost and poor availability of mental health treatment, many individuals do not seek assistance for mental health problems [3]. Consequently, it is important to consider the application of alternative and complimentary therapies regarding mental health treatment. Martial arts training may be a suitable alternative, as it incorporates unique characteristics including an emphasis on respect, self-regulation and health promotion. Due to this, martial arts training could be viewed as a sports-based mental health intervention that potentially provides an inexpensive alternative to psychological therapy [4]. However, the efficacy of this approach has received little research attention [5].

Existing martial arts research has mostly focused on the physical aspects of martial arts, including physical health benefits and injuries resulting from martial arts practice [6], while few studies have examined whether martial arts training addressed mental health problems or promoted mental health and wellbeing. Several studies report that martial arts training had a positive effect reducing symptoms associated with anxiety and depression. For example: (a) training in tai-chi reduced anxiety and depression compared to a non-treatment condition [7], (b) karate students were less prone to depression compared to reported norms for male college students [8], and (c) a study examining a six-month taekwondo program reported significantly reduced anxiety [9]. Similarly, several studies report martial arts training promotes characteristics associated with wellbeing including: (a) a group of female participants reported higher self-concept compared to a comparison group after studying taekwondo for 8 weeks [10], and (b) a six-month taekwondo program found increased self-esteem following the intervention [9].

A recent meta-analysis examining the effects of martial arts training on mental health examined 14 studies and found that martial arts training had a positive effect on mental health outcomes ([name], [name] & [name] The effect of martial arts training on mental health outcomes: a systematic review and metaanalysis, Under review). The study found that martial arts training had a medium effect size regarding reducing internalising mental health problems, such as anxiety and depression; and a small effect size regarding increasing wellbeing.

However, despite generally positive findings the research base examining the psychological effects of the martial arts training exhibits significant methodological problems [11, 12]. These include definitional and conceptual issues, a reliance on cross-sectional research designs, small sample sizes, self-selection effects, the use of self-report measures without third party corroboration, absence of follow-up measures, not accounting for demographic differences such as gender, and issues controlling for the role of the instructor. These issues may limit the generalisability of findings and suggest uncertainty regarding the validity and reliability of previous research.

This study seeks to examine the relationship between martial arts training and mental health outcomes, while addressing the methodological limitations of previous studies. The intervention examined by the study is a bespoke programme based primarily on the martial art taekwondo and incorporating psycho-education developed for the intervention. Importantly, this study aims to examine the efficacy of a martial arts based therapeutic intervention to improve mental health outcomes.

## Methods/design

### Study design

This study is a 10-week secondary school-based intervention and will be evaluated using a randomised controlled trial. Ethics approval has been sought and obtained from an Australian University Human Research Ethics Committee, the New South Wales (NSW) Department of Education, and the Catholic Education Diocese of Parramatta. The study is registered with the Australian and New Zealand Clinical Trials Registry (ACTRN12618001405202). The study protocol was also reviewed externally by school psychologists employed by the NSW Department of Education.

Researchers will conduct baseline assessments at participating schools after the initial recruitment processes. Following baseline assessments and randomisation, the intervention group will receive the intervention after which post-intervention assessment will be conducted. A 12-week post-intervention (follow-up) assessment will also be conducted. The control group will receive the same intervention program after the first post-intervention assessment and will not be measured at follow-up. The design, conduct and reporting of this study will adhere to the Consolidation Standards of Reporting Trials (CONSORT) guidelines for a randomised controlled trial [13]. Participants and caregivers will provide written informed consent.

### Sample size calculation

Power calculations were conducted to determine the sample size required to detect changes in mental health related outcomes resulting from martial arts training. Statistical power calculations assumed baseline-post-test expected effect size gains of *d* = 0.3, and were based on 90% power with alpha levels set at *p* < 0.05. The minimum completion sample size was calculated as *n* = 234 (intervention group: *n* = 117, control group: *n* = 117). As participant drop-out rates of 20% are common in randomised controlled trials [14], the maximum proposed sample size was *n* = 293 (intervention group: *n* = 147, control group: *n* = 146).

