### Recruitment and study participants

To be eligible to participate in the study, schools must be government or catholic secondary schools in NSW, Australia. All eligible schools (*n* = 140) will be sent an initial email with an invitation to participate in the study. Schools that respond to the initial email will be pooled and receive a follow up call in random order from the project researchers to discuss whether they would like to participate in the study. The first five schools that demonstrate interest will then be recruited into the study.

Inclusion criteria for participation in the study includes: (a) participants are currently enrolled in grades 7 or 8, and (b) participants are within an age range 11–14 years. Exclusion criteria: concurrent martial arts training will exclude participation in the study, however prior experience of martial arts training is not an exclusion criteria. All students at participating schools who meet these criteria will be invited to participate in the study. Participant and caregiver information and consent forms will be provided to students. Two follow-up letters will be sent subsequently at 2 week intervals. Students who respond to the invitation will be pooled and randomly allocated into the study, or not included in the study.

Randomisation into intervention and control group will occur after baseline assessments. A simple computer algorithm will be used to randomly allocate participants into intervention or control groups. This will be performed by a researcher not directly involved in the study. Figure 1 provides a flowchart of the timeline for the study.

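### The stated inputs call for 234 completers per arm, not 234 in total; 117 per arm gives about 63% power for a between-arm d = 0.3, not 90%

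*Protocol article*

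**What the plan says.** The Sample size calculation section gives its inputs: "Statistical power calculations assumed baseline-post-test expected effect size gains of *d* = 0.3", and these "were based on 90% power with alpha levels set at *p* < 0.05". It does not say whether the test is one- or two-sided, and it gives no correlation between baseline and post-test.

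The result follows: "The minimum completion sample size was calculated as *n* = 234 (intervention group: *n* = 117, control group: *n* = 117". After an allowance for 20% drop-out, "the maximum proposed sample size was *n* = 293 (intervention group: *n* = 147, control group: *n* = 146". The abstract repeats the inflated figure as the outcome of the power calculation: "Power calculations indicate a maximum sample size of *n* = 293 is required".

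The trial is a parallel two-arm comparison. Under Recruitment and study participants: "A simple computer algorithm will be used to randomly allocate participants into intervention or control groups". The Study design section adds that controls are not measured at follow-up, so the randomised comparison rests on two occasions, baseline and post-intervention.

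**The concern.** An effect of 0.3 SD is small, and at 90% power a two-arm trial needs well over 200 completers in each arm to detect it. The section arrives at 117 per arm. Two familiar formulas, neither with a correlation term, return its numbers: the two-sample formula gives 234 per arm, and the one-group pre-post formula gives 117. The first would mean that a per-arm number was taken as the total. The second would fit the wording about gains, but it describes change within one group, not a difference between randomised groups.

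If the 90% is wrong, the trial runs a much larger risk of missing the effect it was designed to find than its readers are told. A null result would then be open to being read as good evidence against d = 0.3. This matters more because the Background faults earlier studies for small samples and the Conclusion claims unmatched scale and possible influence on policy.

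**Working it through.** **Inputs**
- From Sample size calculation: d = 0.3 (so SD = 1), power 90% (z = 1.2816), alpha 0.05, 117 completers per arm, drop-out 20%.
- Assumed: two-sided test (z = 1.96). One-sided is also tried.

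**1. The plan's own figures**
- Drop-out: 234/(1 − 0.20) = 292.5, rounded up to 293. This reproduces.
- Completers for two independent arms: n per arm = 2(1.96 + 1.2816)²/0.3² = 233.5, so **234 per arm, 468 in total** (t-test: 234.5, so 235 per arm). The stated total of 234 does not reproduce.
- One-group pre-post formula: (1.96 + 1.2816)²/0.3² = 116.7, so 117. This matches the stated arm size but not the design.
- Other settings for two arms: one-sided alpha at 90% power gives 191 per arm; 80% power gives 175 per arm two-sided or 138 one-sided. None gives 117.

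**2. Power with the stated numbers, between-arm d = 0.3**

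Normal approximation at 117 per arm: 0.3 × √(117/2) = 2.295; 2.295 − 1.96 = 0.335; Φ(0.335) = 63.1%.

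| Case | Power (t-test) |
|---|---|
| 117 per arm, two-sided | 62.7% |
| 117 per arm, one-sided | 74.0% |
| 146 per arm (no drop-out), two-sided | 72.4% |
| 147 per arm (no drop-out), two-sided | 72.7% |

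**3. Detectable effect at 117 per arm, two-sided**

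(1.96 + 1.2816) × √(2/117) = 0.42 by normal approximation, about 0.43 by t-test, for 90% power. For 80% power it is about 0.37.

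**4. What correlation would rescue the 90%?**

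Let r be the baseline to post-test correlation, with d on the raw-score SD.
- ANCOVA: 233.5(1 − r²) ≤ 117, so r must be at least about 0.71.
- Change score, equivalent to group-by-time with two occasions: 233.5 × 2(1 − r) ≤ 117, so r must be at least about 0.75.

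Power at 117 per arm (normal approximation, two-sided):

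| r | ANCOVA | Change score |
|---|---|---|
| 0.5 | 75% | 63% |
| 0.6 | 82% | 73% |
| 0.7 | 89% | 84% |

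If d is standardised on the gain scores themselves, change-score power is 63% whatever r is, because the correlation is already in the denominator of d.

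**5. Repeated-measures interaction**

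A gain difference of 0.3 SD over two occasions corresponds to f = 0.075; at r = 0.5 this needs 470 in total. Using f = 0.15 gives 236 in total only at r = 0, and that stands for a gain difference of 0.6 SD, twice the stated effect.

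**6. Size that would deliver the stated power**

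468 completers; 468/0.8 = 585 randomised.

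**The case against.** The strongest reply is that a comparison of post-test means alone is not the planned analysis. The Statistical methods section plans repeated-measures ANOVA and MANOVA with demographic covariates, and a design that uses the baseline can need fewer participants. The section is also one paragraph of a condensed article, so a correlation or software setting may sit in a fuller document, and its absence here proves little. In addition, two-sidedness is an assumption, and how the figure arose is not shown.

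Part of this stands. The 63% is the power for the inputs as printed, and it should carry the condition on r. Two-sidedness has to be labelled as assumed, and the origin of the slip remains an inference.

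It does not restore the 90%. A one-sided test reaches only 74.0%. The planned analysis does not name the baseline score as a covariate, so the change-score figures are the closer ones, and they reach 90% only at r of about 0.75. The wording about gains points, if anything, to the scale on which r gives no help. Both printed numbers also come straight from formulas without a correlation term, which makes an undisclosed correlation an unlikely source. The objection is to a result that does not follow from its printed inputs, not to a missing detail.

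**Conclusion.** The point holds. For two independent arms, d = 0.3, two-sided alpha 0.05 and 90% power, the requirement is 234 completers per arm. The planned 117 per arm gives about 63% power, a type II error of about 37% against the 10% claimed, and gives 90% power only for d of about 0.43.

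This rests on d = 0.3 being the between-arm difference and on no credit for the baseline. With credit, and with d on the raw-score SD, power at r between 0.5 and 0.7 is 75% to 89% (ANCOVA) or 63% to 84% (change score). Nothing in the article states that d is on that scale or that r reaches the 0.71 or 0.75 needed. The abstract's 293 is the same error carried forward through a correct drop-out step, not a second one.

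**What to change.** Keep 234 completers and 293 randomised, and correct what is claimed for them. Either of two routes will do:

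- **Restate the power.** In Sample size calculation, say that 117 completers per arm give about 63% power for a between-arm d = 0.3 at two-sided 0.05, and 90% power for d of about 0.43.
- **Base it on the adjusted contrast.** Define the target as the baseline-adjusted difference between arms, say on which SD d is scaled, state and justify the assumed correlation, and give the range: ANCOVA power 75%, 82% and 89% at r = 0.5, 0.6 and 0.7. The analysis must then include the baseline score as a covariate.

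Under either route, state the sidedness and reword the abstract sentence so that 293 is no longer presented as the number required for 90% power at d = 0.3.

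The cost is rewording in two places and a less favourable stated power. No extra participants are needed. Holding to 90% power for an unadjusted d = 0.3 would instead take 585 randomised, about twice the planned number.

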### Recruitment and study participants

To be eligible to participate in the study, schools must be government or catholic secondary schools in NSW, Australia. All eligible schools (*n* = 140) will be sent an initial email with an invitation to participate in the study. Schools that respond to the initial email will be pooled and receive a follow up call in random order from the project researchers to discuss whether they would like to participate in the study. The first five schools that demonstrate interest will then be recruited into the study.

Inclusion criteria for participation in the study includes: (a) participants are currently enrolled in grades 7 or 8, and (b) participants are within an age range 11–14 years. Exclusion criteria: concurrent martial arts training will exclude participation in the study, however prior experience of martial arts training is not an exclusion criteria. All students at participating schools who meet these criteria will be invited to participate in the study. Participant and caregiver information and consent forms will be provided to students. Two follow-up letters will be sent subsequently at 2 week intervals. Students who respond to the invitation will be pooled and randomly allocated into the study, or not included in the study.

Randomisation into intervention and control group will occur after baseline assessments. A simple computer algorithm will be used to randomly allocate participants into intervention or control groups. This will be performed by a researcher not directly involved in the study. Figure 1 provides a flowchart of the timeline for the study.

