### Intervention design

#### Intervention description

The intervention will be delivered in a face to face group format onsite at participating schools. The intervention will be 10 × 50–60 min sessions, once per week for 10 weeks. Each intervention session will include:
Psycho-education – guided group based discussion. Topics include respect, goal-setting, self-concept and self-esteem, courage, resilience, bullying and peer pressure, self-care and caring for others, values, and, optimism and hope;Warm up – including jogging, star jumps, push ups, and sit ups;Stretching – including hamstring stretch, triceps stretch, figure four stretch, butterfly stretch, lunging hip flexor stretch, knee to chest stretch, and standing quad stretch; and,Technical practice – including stances, blocks, punching, and kicking.

Additionally, intervention sessions intermittently include (alternated throughout the program):
(e)Patterns practice – a pattern is a choreographed sequence of movements consisting of combinations of blocks, kicks, and punches performed as though defending against one or more imaginary opponents;(f)Sparring – based on tai-chi sticking hands exercise (which has been included as an alternative to traditional martial arts sparring); and(g)Meditation – based on breath focusing exercise.

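### Allocation is not stated to be balanced within the five delivery schools, and school is not in the analysis; a within-school draw plus a school factor is a small gain at almost no cost

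*Protocol article*

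**What the plan says.** Four parts of the protocol article bear on this point.

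- **Allocation** (Recruitment and study participants): "A simple computer algorithm will be used to randomly allocate participants into intervention or control groups". A researcher outside the study team runs it. On timing, "Randomisation into intervention and control group will occur after baseline assessments". The section mentions no blocks, no school stratum and no fixed arm size.
- **Schools and delivery**: "The first five schools that demonstrate interest will then be recruited into the study" (same section), and "The intervention will be delivered in a face to face group format onsite at participating schools" (Intervention description). Controls wait: "The control group will receive the same intervention program after the first post-intervention assessment and will not be measured at follow-up" (Study design). Each school's split therefore sets the number of pupils treated first and the number treated later.
- **Planned numbers** (Sample size calculation): the dropout-inflated maximum of 293 is divided as "intervention group: *n* = 147, control group: *n* = 146".
- **Analysis** (Statistical methods): repeated-measures ANOVA and MANOVA, with age, grade, sex, socio-economic status and cultural background as covariates. School is not listed.

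**The concern.** School is the place of delivery, yet neither the stated allocation nor the stated covariate list uses it. If the draw ignores school, chance decides how many pupils in each school are treated first and how many wait, and so how the school mix differs between the arms. With only five schools, such differences need not be negligible. Part of the random error in the treatment contrast then comes from a source that the design could remove. A school term added later recovers most of this but not all, and it cannot change the group sizes that the draw produced.

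What is at stake is a little precision and orderly group sizes. The validity of the comparison is not in question.

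**Working it through.** **Inputs from the protocol article:** 293 pupils planned (147 and 146), 234 completers (117 per arm), 20% dropout, d = 0.3, five schools.

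**Assumptions not in the article:** schools of equal size (59, 59, 59, 58, 58); school ICC of 0.01 to 0.10; outcome SD of 1.

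**1. The plan's own figure.** 234 / 0.8 = 292.5, rounded up to 293; 117 / 0.8 = 146.25, rounded up to 147. The stated maximum is reproduced.

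**2. Arm totals.** Two readings of the text ignore school.
- *Independent 1:1 assignment.* The arm size is Binomial(293, 0.5), with SD = √293 / 2 = 8.6. The probability of 147/146, either way round, is 9.3%, and the 95% range of one arm is 130 to 163.
- *One shuffled list cut at 147.* The totals are exact.

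The precision cost of uneven totals is slight. At 163/130 the variance ratio is (1/163 + 1/130) / (1/147 + 1/146) = 1.013. Taking the plan's 90% power at 117/117 as given (SD scaled to 0.7071), 132/102 completers give Φ(0.3 / (0.7071 × √(1/132 + 1/102)) − 1.96) = 89.6%.

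**3. Splits within schools** (200,000 simulated draws, five equal schools).

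| Reading | Median of largest within-school difference | Some school differs by 10 or more |
|---|---|---|
| Independent assignment | about 12 pupils | 69% |
| Shuffled list cut at 147 | 10 pupils | 54% |

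Under independent assignment, one school of 59 has a 95% range of 22 to 37 pupils in the intervention group. A fixed overall total does not remove the drift within schools.

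**4. Contribution of school mix to the contrast.** For a post-test comparison without baseline adjustment, 234 completers and five equal schools, SD ≈ √(ICC × (4/234) × (4/5)). The factor 4/5 arises because only contrasts among the five schools matter; their common mean cancels.

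| ICC (assumed) | SD | 1.96 × SD |
|---|---|---|
| 0.01 | 0.012 | ±0.02 |
| 0.05 | 0.026 | ±0.05 |
| 0.10 | 0.037 | ±0.07 |

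Simulation gives the same SDs under both readings; its 95% percentiles run from ±0.024 to ±0.076, so the tails are slightly wider than 1.96 SD. Relative to the sampling variance of the contrast, 4/234, the school part is 0.8 × ICC, or 0.8% to 8%.

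**5. Loss if school is only adjusted for afterwards.** In a school with n pupils, x of them in the intervention group, the information on the school-adjusted contrast is proportional to x(n − x)/n. Under independent assignment its mean is (n − 1)/4, against n/4 for an even split. Summed over five schools, efficiency is (293 − 5)/293 = 0.983 for those randomised and (234 − 5)/234 = 0.979 for completers. The loss is about 2%.

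**6. After the change.** Each school splits to within one pupil (59 as 30/29, 58 as 29/29). The arms then differ by at most the number of odd-sized schools. If the odd places alternate between arms, the assumed sizes give 147/146.

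**The case against.** The case against has real force, and several of its parts stand.

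- **The method is inferred.** The word simple describes the algorithm; the text does not name simple randomisation. A shuffled list cut at 147 fits the wording and gives the planned totals, so the 9.3% figure depends on the reading. A separate draw in each school is not excluded either. A reader might infer a single cross-school pool from "Students who respond to the invitation will be pooled and randomly allocated into the study, or not included in the study", but that sentence concerns selection into the study, not the split into arms.
- **No contradiction on numbers.** A reader might infer that the allocation breaks a promise of 147 and 146. The text introduces those figures with "the maximum proposed sample size was". They are a recruitment target, not a stated output of the algorithm.
- **School mix does not pass straight into the estimate.** Outcomes are also measured at baseline, so stable school differences cancel in the group-by-time comparison and only differences in change remain. Socio-economic status and cultural background may absorb some of the rest. What is left is ordinary random error, which the unadjusted standard error already reflects.
- **Even groups are not promised.** The article sets no group-size limit, does not say that each school has one group, and gives no school sizes. Nothing in it shows that a group of 22 or 37 would be unworkable.
- **Condensation.** A journal article may leave blocking and strata to the full protocol.

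The last point does not dispose of the matter. The article does state an allocation method and a covariate list, and school appears in neither. On both readings that ignore school, the groups within schools drift by similar amounts.

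**Conclusion.** The point holds as a minor design improvement. As written, the allocation guarantees neither near-equal arms nor near-equal groups within schools, and the listed covariates omit school. With five equal schools, the median of the largest within-school difference is 10 to 12 pupils. In a post-test contrast without baseline adjustment, school mix adds at most about ±0.02 to ±0.07 SD for an ICC of 0.01 to 0.10, and less in the planned group-by-time comparison. About 2% efficiency is lost if school enters only at the analysis.

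These sizes rest on assumed school sizes, an assumed ICC range and the reading that allocation is not stratified by school. The documents do not support a claim of bias, of a conflict with the sample size section, or of a material loss of power: even a 132/102 split of completers costs less than one percentage point.

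**What to change.** In Recruitment and study participants, state that the same independent researcher allocates pupils separately within each school, by an exact half split of that school's completed baseline list or by permuted blocks. In Statistical methods, add school as a factor in the outcome models so that the analysis follows the allocation. If allocation is already done by school, saying so and adding the factor is enough.

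Because randomisation follows baseline, each school's list exists before its draw, even if the five schools start at different times. The whole list is drawn at once, so balancing it gives nobody a sequence to predict. The cost is one sentence in each section, a few lines of code and four degrees of freedom for a five-level factor. No extra pupils, staff or assessments are needed.
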